##### Additional measures/covariates

*Baseline risk:* during the screening process, our clinician team codes clients as green (low risk), orange (medium risk), or red (high risk) (Appendix B in Supplementary Material), chiefly in order to match clients with appropriately skilled and experienced volunteers. Demographics: Age, living situation, education, mental illness diagnoses, and psychotropic medication use will be obtained at baseline. *Digital Literacy:* We will systematically measure digital literacy using the Technology in Geriatric Psychiatry scale, which is a 14-item questionnaire about patients' access to technological devices, comfort or familiarity with software, availability of family members who can assist in setting up technology, interest in learning to use video conferencing software, and interest in receiving support via videoconferencing. This scale was developed by co-investigator [name] from Harvard University and is currently being validated in another study.

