Currently, global healthcare systems are overburdened, with professionals increasingly becoming burnt out, reassigned, or infected (17, 18). Additionally, most experts agree that a second wave of infection will occur in the fall of 2020 (19), thus implementing community-based volunteer interventions could aid current mental health support services by preventing the development or worsening of mental health issues. For example, in India, a successful mental health intervention with lay volunteers improved depression and other psychiatric symptoms in older adults by providing problem-solving strategies, health education, and assistance in accessing medical and social programs (20). Indeed, not all telehealth modalities may be accessible to older adults (21); one survey found that only 10% used the internet, while 72% owned a cell phone (22). In the context of COVID-19, many telehealth interventions requiring advanced digital literacy are likely unfeasible for rapid implementation due to a lack of infrastructure, training, and low rates of digital literacy in older adults (23). Given these limitations, telephone-based care is likely able to serve the largest proportion of older adults. Thus, we have started a novel volunteer-based telehealth intervention program for older adults (TIP-OA) in Montreal, Canada. The objective of the study is to assess the efficacy of this program by:

Evaluating the effects on perceived stress, fear related to COVID-19, symptoms of depression and anxiety in older adults (i.e., clients), as well as the effects on mental healthcare utilization.Comparing clients' mental health outcomes based on baseline risk (i.e., low, medium, or high risk).Analyzing the experiences of clients, clinicians, volunteers, and organizers/stakeholders involved in the program using semi-structured interviews and focus groups.

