#### Telehealth Intervention Program for Older Adults (TIP-OA)

#### Recruitment and Training of Volunteers

Volunteers are recruited (1) using an advertisement circulated on social media; (2) through direct recruitment of medical, social work, psychology, and nursing students from McGill University; (3) from the research and clinical teams' social networks; and (4) through the Jewish General Hospital (JGH) Foundation and Auxiliary, a volunteer non-profit organization. Interested individuals are rigorously screened and interviewed using Zoom^TM^, a widely used video conferencing platform. Selected inclusion criteria are the ability to (1) commit for a minimum of 3-months; (2) provide this service to 3-5 clients; and (3) call each client at least once every week. Applicants with a criminal record or applicants who refuse to submit to a background check are excluded from volunteering.

Members of the volunteer management team stratify volunteers according to past volunteering and clinical experience(s) (Appendix A in Supplementary Material). Two trainers facilitate two weekly 2-h training sessions over Zoom^TM^, to a maximum of five volunteers per session (please contact [contact] for more information regarding the training design and/or manual). The initial virtual training was provided in kind collaboration with the Touch-Volunteers in Partnership (ViP) program at the Jewish General Hospital. The Touch ViP program was created through a participatory mixed-methods study, which engaged persons living with mental health conditions, their families, and mental health professionals over 3 years to support recovery-oriented practices (24, 25). The Touch Volunteer Manual, originally designed for in-patient services, was adapted for telehealth and is provided to TIP-OA through the *What connects us-Ce qui nous lie project* Dementia Community Investment fund (1920-HQ-000092), to support the aim to create a web of inter-sectoral resources and decrease stigma. In addition to the stratified matching, the program has been further modified for TIP-OA to address the needs of older adults during COVID-19 with feedback from trainers, clinicians, and volunteers.

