### Selection/Treatment of Subjects

The first 200 TIP-OA clients who provide informed consent will participate in data collection for research.

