### Data Analysis

#### Quantitative Analysis

Descriptive statistics for continuous variables will include means and standard deviations, while categorical variables will be summarized using frequencies and proportions. A within-subjects repeated measure analysis of variance (ANOVA) will be conducted for the PSS (primary outcome), COVID Fear Scale, PHQ-9, GAD-7, and mental healthcare utilization (secondary outcomes) to assess differences in measures between baseline and the 8-week follow-up between groups with different baseline risk (low, medium, and high risk). Additional analysis of covariance (ANCOVAs) will control for variables that differ between groups at baseline. We will use LOCF to handle missing data that results from study attrition. Although we have found it extremely rare to be missing baseline data when, for example, a participant answers all but one question on a measure, in any such case we will exclude the participant's data for that measure. All ANOVAS will be tested at two-tailed alpha = 0.05. Linear mixed effect regression models, adjusting for age and sex, will analyze the effect of TIP-OA on all outcomes (PSS, COVID Fear Scale, PHQ-9, GAD-7, and mental healthcare utilization) collected at baseline and 8-week follow-up. We will perform additional linear mixed effect regression models accounting for a larger group of important variables such as client referral source (e.g., referred from clinic vs. self-referred) and cognitive functioning (e.g., suspected mild dementia vs. no suspected mild dementia) on mental health outcomes. Variable selection in linear mixed effect model (32) will be used to select important fixed effect covariates as they relate to the outcome. The fixed effect point estimates and corresponding confidence intervals and *p*-values will be computed. Additional subgroup analyses will also compare the primary outcome (PSS) between important subgroups [e.g., referral source (referred from clinic vs. self-referred) and cognitive functioning (suspected mild dementia vs. no suspected mild dementia)]. Analyses will be run using R statistical software.

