## Results—Early Experience

As of October 15th, 2020, 150 volunteers have been trained to provide TIP-OA to 305 older clients. Final research ethics approval has been provided and we will consecutively recruit 200 clients for quantitative data collection. After 8-weeks, 16 volunteers and eight clinicians will be consecutively selected for Zoom^TM^ focus groups, and 25 clients, 15 volunteers, and 10 stakeholders will be selected in the same manner for semi-structured interviews on Zoom^TM^.

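### The stated ANOVA and ANCOVAs make no allowance for clients who share a volunteer, and matching by risk color ties the risk-group comparison to volunteer tier

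*Protocol article*

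**What the plan says.** **Who delivers the intervention.** Under Recruitment and Training of Volunteers, applicants must be able to "provide this service to 3-5 clients". The same section says: "Members of the volunteer management team stratify volunteers according to past volunteering and clinical experience(s"). Results—Early Experience reports that "150 volunteers have been trained to provide TIP-OA to 305 older clients".

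**How clients reach volunteers.** Under Additional measures/covariates, the risk color is assigned "chiefly in order to match clients with appropriately skilled and experienced volunteers". Client Referrals, Screening and Matching confirms that clients are allocated to volunteers by category each week. Volunteer Support and Quality Assurance adds that volunteers coded red are particularly urged to use the follow-up meetings for extra support.

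**What is analyzed.** The second objective in the Introduction is "Comparing clients' mental health outcomes based on baseline risk (i.e., low, medium, or high risk"). Under Quantitative Analysis, "A within-subjects repeated measure analysis of variance (ANOVA) will be conducted for the PSS (primary outcome") and for the secondary outcomes, to compare change from baseline to 8 weeks between the three risk groups. ANCOVAs then adjust for variables that differ between groups at baseline. "All ANOVAS will be tested at two-tailed alpha = 0.05". Linear mixed models adjust for age and sex, and further models add covariates such as referral source and suspected mild dementia. The random effects of these models are not given. No analysis names the volunteer or the volunteer's experience level.

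**Sample.** "The first 200 TIP-OA clients who provide informed consent will participate in data collection for research".

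**The concern.** The volunteer is the active ingredient here. Clients called by the same person may change in similar ways because that person is more or less skilled, persistent or well informed. A test that treats those clients as independent then has standard errors that are too small and rejects more often than its nominal 5%.

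The second issue is separate. Color describes the client, and it also steers which kind of volunteer the client gets and how strongly that volunteer is pointed to support. If high-risk clients change more, or less, than low-risk clients, the cause could be their risk, their volunteers or both. The article hopes to extend the program across Canada and internationally, so a statement that it works better or worse in high-risk seniors could shape who is offered it.

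**Working it through.** **Inputs from the article**
- Nominal alpha 0.05, two-sided (Quantitative Analysis).
- 200 research clients (Selection/Treatment of Subjects).
- Reported mean caseload: 305/150 = 2.03 (Results—Early Experience).
- Intended caseload: 3-5 (Recruitment and Training of Volunteers).
- If the 200 research clients were spread over all 150 volunteers: 200/150 = 1.33. That spread is an assumption.

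**Input not in the article**
- ICC of change within volunteer. It is assumed to be 0.05-0.10, with 0 and 0.20 as outer values.

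The article gives no clustering figure to reproduce. Its sample size rests on precedent, without an effect size, SD, power or ICC.

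**Formulas**, for m clients per volunteer:
- Design effect DE = 1 + (m − 1) × ICC
- Correct SE / naive SE = √DE
- Effective sample size = 200/DE
- True two-sided alpha of a naive test of overall change = 2 × [1 − Φ(1.96/√DE)]

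Example: m = 2.03, ICC 0.10 gives DE = 1 + 1.033 × 0.10 = 1.103, √DE = 1.050 and alpha = 0.062.

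| m | ICC | DE | SE ratio | Effective n | True alpha |
|---|---|---|---|---|---|
| 1.33 | 0.05 | 1.017 | 1.008 | 197 | 0.052 |
| 1.33 | 0.10 | 1.033 | 1.017 | 194 | 0.054 |
| 2.03 | 0.05 | 1.052 | 1.026 | 190 | 0.056 |
| 2.03 | 0.10 | 1.103 | 1.050 | 181 | 0.062 |
| 3 | 0.05 | 1.100 | 1.049 | 182 | 0.062 |
| 3 | 0.10 | 1.200 | 1.095 | 167 | 0.074 |
| 5 | 0.05 | 1.200 | 1.095 | 167 | 0.074 |
| 5 | 0.10 | 1.400 | 1.183 | 143 | 0.098 |

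At ICC 0 every row returns to 200 and 0.05. At ICC 0.20, alpha is 0.074 for m = 2.03 and 0.144 for m = 5.

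The direction of the percentage matters. At 3-5 clients the correct SE is 5-18% larger than the naive one. The naive SE is therefore too small by 1 − 1/1.049 = 4.7% to 1 − 1/1.183 = 15.5%.

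**Three-group test.** With two time points, the risk-by-time test is a one-way ANOVA on change. It was simulated with about 66 clients per group, volunteers nested in risk group and 8,000 runs per setting. Rejection rates at nominal 0.05:
- m = 2: 0.054 (ICC 0.05) and 0.069 (ICC 0.10)
- m = 5: 0.081 and 0.118
- ICC 0: 0.046-0.052 across the caseloads tried

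The large-sample value for this 2-df test is 0.05^(1/DE). For m = 5 that is 0.05^(1/1.2) = 0.082 and 0.05^(1/1.4) = 0.118, in agreement. The risk-group comparison is thus somewhat more exposed than the overall change when caseloads are large.

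**Risk and volunteer tier.** No arithmetic applies; the sections are read together. Volunteers are graded by experience, clients are graded by risk, clients are assigned by grade, and support is emphasized by grade. The ANOVA then compares those same grades. ANCOVA on client variables cannot remove a difference between volunteers. If matching is strict, volunteer tier coincides with color and no model separates them. If matching is loose, separation is possible only when volunteer tier is in the data. Strengths and Limitations says that the study is non-randomized, that the color system is imperfect and that clients may move between categories. It does not mention that volunteer experience moves with color.

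**The case against.** Several counterarguments are sound.

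- **The mixed models may already include the volunteer.** A reader might infer that volunteers are missing from every model. The article does not show this. It leaves the random effects unstated and the covariate list open, and such detail commonly sits in a fuller plan. The point is confined to the ANOVA and ANCOVAs.
- **Inflation is not a fact.** It requires a positive ICC, and the article offers none.
- **The 3-5 figure is a capacity requirement, not an observed load.** The observed mean is 2.03, where the SE effect is about 3-5%. If the 200 spread over all 150 volunteers, it is at most 3.3% even at ICC 0.20. Uneven caseloads would push the other way, but the article does not give their distribution.
- **Matching is part of the program.** Asking how each tier fares under the program as delivered is legitimate, and the second objective does not expressly claim to isolate client risk. This largely stands. What remains is that the article names the comparison by baseline risk alone and nowhere warns that volunteers differ too.
- **Strength of confounding.** It is tempting to call it nearly complete. The appendices that define the volunteer and client strata are not shown, color is said to serve matching chiefly rather than solely, the risk assessment is described as flexible, and re-pairing is allowed. The dependence is clear, but its degree is not.

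**Conclusion.** The point holds in limited form. The ANOVA and ANCOVAs, as described, make no allowance for shared volunteers. Under an assumed ICC of 0.05-0.10, the true alpha for overall change is about 0.056-0.062 at the reported caseload and about 0.06-0.10 at 3-5 clients each. It is nearer 0.05 if the sample spreads over more volunteers, and exactly 0.05 at ICC 0. At the reported caseload this is a small effect.

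The interpretive issue depends on no ICC. By the program's own assignment rule, a difference in change between risk groups reflects client risk together with the matched volunteer tier, in unknown proportion. The overall baseline-to-8-week point estimate is not biased by this matching; only its standard error is in question. Neither part invalidates the study. Both justify an inexpensive improvement.

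**What to change.** 1. Carry volunteer ID and volunteer tier into the analysis data set at each visit. State in advance which volunteer defines the cluster when a client is re-paired.
2. For the tests of change and of risk-group differences, use volunteer-clustered robust standard errors or a mixed model with a volunteer-by-visit random effect. A volunteer intercept alone is not enough, because it is common to both visits and cancels from the change.
3. Define the second objective and its analysis as a comparison of risk tiers together with their matched volunteers, and state that no difference will be attributed to client risk alone. Tabulate volunteer tier against client color, including off-category matches, so that readers can see how tightly the two are linked. Item 2 does not remove this confounding, so both changes are needed.
4. Add a sentence on this to Strengths and Limitations.

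The cost is an ID that those who assign clients to volunteers should already hold, some rewording, and slightly wider intervals: about 3-5% at the reported caseload under the assumed ICC.

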#### Client, Volunteer, and Stakeholder Qualitative Outcome Measures

*Zoom*^*TM*^
*focus groups* will be conducted at an 8-week follow-up with 16 volunteers (eight per group) and eight clinicians/stakeholders, who will be consecutively selected and invited over the phone to participate. Verbal informed consent will be obtained before the start of the focus groups.

*Semi-structured interviews:* 10 different stakeholders (e.g., referring clinicians, clinical team, coordinators, community partners), 15 volunteers, and 25 clients (consecutively selected) will additionally be invited to participate in individual semi-structured interviews, for which verbal informed consent will be obtained. The client interviews will consist of open-ended and guided questions regarding the overall program and its impact on their mental health and well-being (see Appendix C in Supplementary Material). The main purposes of the volunteer and stakeholder focus groups and interviews are to analyze their experiences (including challenges and opportunities encountered) and to assess the strengths, weaknesses, and viability of the program. For example, volunteer focus groups and interviews inquire about the types of issues encountered when dealing with clients, their ability to provide clients with support, and their experience accessing support from the TIP-OA team. Stakeholder focus groups and interviews include questions about their comprehension of the program procedures, their perception of the program's impact on clients, and their ability to work with the TIP-OA team.

### Data Analysis

#### Quantitative Analysis

Descriptive statistics for continuous variables will include means and standard deviations, while categorical variables will be summarized using frequencies and proportions. A within-subjects repeated measure analysis of variance (ANOVA) will be conducted for the PSS (primary outcome), COVID Fear Scale, PHQ-9, GAD-7, and mental healthcare utilization (secondary outcomes) to assess differences in measures between baseline and the 8-week follow-up between groups with different baseline risk (low, medium, and high risk). Additional analysis of covariance (ANCOVAs) will control for variables that differ between groups at baseline. We will use LOCF to handle missing data that results from study attrition. Although we have found it extremely rare to be missing baseline data when, for example, a participant answers all but one question on a measure, in any such case we will exclude the participant's data for that measure. All ANOVAS will be tested at two-tailed alpha = 0.05. Linear mixed effect regression models, adjusting for age and sex, will analyze the effect of TIP-OA on all outcomes (PSS, COVID Fear Scale, PHQ-9, GAD-7, and mental healthcare utilization) collected at baseline and 8-week follow-up. We will perform additional linear mixed effect regression models accounting for a larger group of important variables such as client referral source (e.g., referred from clinic vs. self-referred) and cognitive functioning (e.g., suspected mild dementia vs. no suspected mild dementia) on mental health outcomes. Variable selection in linear mixed effect model (32) will be used to select important fixed effect covariates as they relate to the outcome. The fixed effect point estimates and corresponding confidence intervals and *p*-values will be computed. Additional subgroup analyses will also compare the primary outcome (PSS) between important subgroups [e.g., referral source (referred from clinic vs. self-referred) and cognitive functioning (suspected mild dementia vs. no suspected mild dementia)]. Analyses will be run using R statistical software.

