#### Client Referrals, Screening and Matching

Clients are either self-referred or referred from the JGH (COVID-19 inpatient units or the geriatric psychiatry clinic), long-term care facilities, local primary care clinics, or community organizations in the west-central Montreal healthcare/administrative catchment region (which represents over 500,000 residents from diverse ethnic backgrounds). Interested clients and clinicians can call our voicemail number, send an email, or fill out a form on our website to refer to our program. Included clients are consenting older adults (age ≥ 60) living in Montreal. Excluded individuals (1) are actively suicidal, (2) have a severe hearing impairment or other disability preventing the use of a phone, or (3) are suffering from moderate or severe dementia, as determined by clinical judgment (e.g., based on client history and/or past memory testing), or (4) are unable or unwilling to provide informed consent.

At intake, the screening clinician or trainee (e.g., in psychiatry, social work, psychology) spends 20–30 min on the phone with each client to collect basic demographic information and perform an informal clinical assessment regarding the client's level of cognitive functioning (coded as having suspected mild dementia or not). In cases where the client was referred from a clinic, our clinical team receives information from the referring clinician regarding the clients' cognitive and overall functioning. The screening clinician also assesses the client's level of risk and the complexity of their case, conducting a brief assessment developed primarily from Culo's paper (26) and national guidelines pertaining to seniors' mental health (27). This risk assessment is flexible and allows for the consideration of factors that are not included in the assessment, but that may hamper communication between the client and volunteer. The team then stratifies clients into categories based on case complexity and the initial risk assessment (Appendix B in Supplementary Material). Although we only assess case complexity at baseline, communication with volunteers through various channels (see section Volunteer Support and Quality Assurance) typically informs us of client mobility between categories. Following client screening and categorization, a clinician and volunteer manager assign clients to newly trained volunteers according to their assigned categories on a weekly basis.

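### Comparing change across intake risk colours cannot separate greater benefit from regression to the mean, so the result should be limited to description

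*Protocol article*

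**What the plan says.** The Introduction of the protocol article sets out three ways in which the study will assess efficacy. The second is "Comparing clients' mental health outcomes based on baseline risk (i.e., low, medium, or high risk".

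The section on client referrals, screening and matching describes the grouping: "The screening clinician also assesses the client's level of risk and the complexity of their case", and then "The team then stratifies clients into categories based on case complexity and the initial risk assessment". The section on additional measures and covariates confirms the timing and the labels: "during the screening process, our clinician team codes clients as green (low risk), orange (medium risk), or red (high risk".

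Under Quantitative Analysis, the repeated-measures ANOVA is used "to assess differences in measures between baseline and the 8-week follow-up between groups with different baseline risk (low, medium, and high risk", at two-tailed alpha 0.05. It is followed by this sentence: "Additional analysis of covariance (ANCOVAs) will control for variables that differ between groups at baseline". The covariates of those ANCOVAs are not named.

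The first 200 consenting clients are studied, and all receive the calls. Strengths and Limitations concedes that the design is observational and non-randomised and that the risk categories are imperfect. It also says that risk was rated only at baseline and that clients may have changed category during the eight weeks. It does not mention regression to the mean.

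**The concern.** With two time points, the time-by-risk test in a repeated-measures ANOVA is a test of equal mean change in the three colours. The colour is a clinician's rating made at the start of follow-up. If part of that rating reflects how distressed the client happens to be at that moment, and the baseline score reflects the same distress, red clients are partly selected for high starting scores. Those scores tend to fall back by week 8 whatever the calls do.

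This is not the usual one-arm problem. A pandemic trend common to all clients cancels when colours are compared. Regression to the mean does not cancel, because its size differs by colour.

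Adjusting for the baseline score is not a safe remedy. If colour carries more information about lasting severity than about passing distress, red and green clients with the same baseline score have different expected week-8 scores, and red clients look as if they did worse.

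The comparison sits under an efficacy aim. A significant result would therefore naturally be read as the programme helping high-risk clients most, or least, and could influence who is offered it.

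**Working it through.** The article gives no effect size, SD, power or colour distribution, so there is no stated figure to reproduce. The check asks what the planned tests do when the calls help every colour equally.

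**Inputs from the article:** 200 clients, three colours, baseline and week 8, two-sided alpha 0.05, no untreated group.

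**Assumed inputs:** PSS SD 8, a true fall of 2 points in every colour, and a 40/35/25% split into green, orange and red.

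**Model.** In SD units, baseline = T + S0 and week 8 = T + S1 minus a constant. T is lasting severity with variance ρ. S0 and S1 are independent passing states with variance 1 − ρ. Colour is the ranked value of C = aT + bS0 + noise (noise SD 1).

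**Direction of bias.**
- Change analysis: Cov(C, S1 − S0) = −b(1 − ρ). This is zero only if b = 0; otherwise red appears to improve more.
- ANCOVA on the baseline score: Cov(C, week 8) − ρ·Cov(C, baseline) = aρ − ρ[aρ + b(1 − ρ)] = ρ(1 − ρ)(a − b). Red looks worse if a > b, there is no bias if a = b, and red looks better if b > a.

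**Hand check at ρ = 0.5, a = 1, b = 0.5.** Var(C) = 0.5 + 0.25 × 0.5 + 1 = 1.625, so its SD is 1.275. In SD units, the mean of C is 1.271 in the top 25% and −0.966 in the bottom 40%, a gap of 2.237. The spurious red-minus-green change is 8 × (−0.25/1.275) × 2.237 = −3.51 PSS points. Simulation gave −3.52.

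**Simulation** (3,000 studies per cell; ranges cover ρ from 0.5 to 0.8; differences are red minus green in PSS points, listed from ρ = 0.5 to ρ = 0.8):

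| Weights a, b | Spurious difference in change | ANOVA falsely significant | Baseline-adjusted difference | ANCOVA falsely significant |
|---|---|---|---|---|
| 1, 0 | 0 | about 5% | +4.2 to +3.0 | 76–86% |
| 1, 0.25 | −1.8 to −0.7 | 9–19% | +3.4 to +2.3 | 51–62% |
| 1, 0.5 | −3.5 to −1.3 | 23–60% | +2.4 to +1.6 | 25–31% |
| 1, 1 | −6.3 to −2.6 | 73–99% | about 0 | about 5% |
| 0.5, 1 | −7.0 to −3.0 | 88–99.7% | −2.4 to −1.5 | 27–33% |
| 0, 1 | −7.3 to −3.3 | 92–99.9% | −4.2 to −2.7 | about 80–87% |

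**Second set of assumptions.** This version adds measurement error: stable share of variance 0.5–0.7, transient share 0.35–0.15 and error share 0.15. The colour mix is 50/30/20, and colour correlates 0.5–0.7 with the state it is based on. The ANOVA false-positive rate is:
- about 5% if colour is purely stable;
- 9–40% with passing distress at half the weight of lasting severity;
- 18–87% at equal weight;
- 42–99% at double weight.

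At half weight the spurious difference in change is about −0.8 to −2.9 points, while the baseline-adjusted ANCOVA is falsely significant in about 29–67% of studies with red worse. The two analyses then point in opposite directions on the same data.

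**A tempting decision rule.** One could claim a difference only if both analyses are significant in the same direction. Under the second set of assumptions, this rule is falsely positive in at most about 10% of studies up to double weight. The rate rises to 14–46% at four times the weight and 46–89% if colour is purely transient. If colour is purely stable, so that the ANOVA is valid, power for a true 4-point difference falls from 69–91% with the ANOVA alone to about 0–18%.

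**The case against.** The strongest reply is that nothing shown says the colours capture a passing crisis. They rest on risk and case complexity, may take account of anything that hampers communication, and serve chiefly to match clients with volunteers. Actively suicidal people are excluded. The PSS looks back over a month, which dilutes a momentary crisis. LOCF, which was not modelled, would shrink apparent falls. All of this bears on size, and it stands: without Appendix B the loadings are unknown. It does not remove the problem, since the article itself allows that clients may change category within eight weeks.

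Second, the ANCOVA covariates are not named. The section on additional measures lists demographics, diagnoses, medication and digital literacy, and a repeated-measures ANOVA already contains the baseline score as an outcome. A reader might infer that the ANCOVA will certainly adjust for baseline score and so contradict the ANOVA. The article does not establish that. The stated rule would include the baseline score if it differs by colour, but the opposite error also requires colour to lean towards lasting severity.

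Third, a reader might say that the plan leaves the two analyses without any order. The ANOVA comes first and the ANCOVAs are called additional, and a fuller rule could sit in an analysis plan that is not shown. That charge is not pressed here.

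Fourth, the article concedes a non-randomised design and makes no claim that one colour benefits more. Both are true. However, the concession is general, and the comparison is listed as a means of assessing efficacy with no limit on its interpretation. The point rests on the comparison that the article itself fixes, not on something it omits.

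**Conclusion.** The concern holds in a limited form. A difference in change between risk colours cannot be attributed to differential benefit, because colour is assigned at intake and no colour has untreated clients. The change analysis favours high-risk clients whenever colour shares any passing distress with the baseline score. The ANCOVA errs the other way only if it includes the baseline score and colour mainly reflects lasting severity.

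The size cannot be fixed from the article. Across the assumed loadings, the ANOVA's false-positive rate runs from about 5%, where it is valid, through 9–40% in the half-weight scenario with measurement error, to above 90% where colour is mainly transient. These figures depend on the assumed SD, colour mix, variance shares and weights.

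It would go too far to conclude that any difference found will be an artefact, or that the two planned analyses must disagree.

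**What to change.** Add to Quantitative Analysis, in substance: the time-by-risk ANOVA and the accompanying ANCOVAs describe how scores change in each risk colour; they will not be taken as evidence that the programme works better or worse in any risk group; regression to the mean, arising because colour is assigned from an intake assessment, is an alternative explanation for any difference; and the change within each colour will be reported with its confidence interval.

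Do not replace this with a rule that both analyses must be significant. As shown above, that rule fails when colour is mostly transient and loses nearly all power when colour is stable.

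The cost is a few sentences and three intervals per outcome from data already planned. The real price is that the study gives up a claim of differential benefit by risk, which this design cannot support. Separating the two explanations would need a comparison group graded into the same colours; the waitlist-controlled pilot that the article mentions as a future possibility could provide one.
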